### Sample size calculation

We based our sample size calculation on fat-free mass (FFM) data of a previously published randomized controlled trial [17]. The mean and standard deviation of FFM were 63.4 and 3.4 (kg) in the intervention group and 66.9 and 4.9 (kg) in the control group. To detect a clinically significant difference in the outcome measures (sleep quality, daytime sleepiness, insomnia, BMI, FFM, body fat mass, waist circumference, waist-to-hip ratio, hip circumference, the visceral fat area, percent body fat, soft lean mass, skeletal muscle mass, extracellular water ratio, and total body water) with an alpha error of 5% and power of 80%, 23 women will be needed in each group. We presume a drop-out rate of 20%, based on clinical study experience, and thus 28 women will be recruited in each group.$$n=\frac{{\left(Z1-\frac{\alpha }{2}+Z1-\beta \right)}^2\left({\sigma}_1^2+{\sigma}_2^2\right)}{\left({\mu}_1-{\mu}_2\right)}$$

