## Outcome measures

### Primary outcomes

The primary outcomes of the study are the differences between the two groups with regard to the changes from baseline values in the following variables: Pittsburgh Sleep Quality Index (PSQI), Epworth Sleepiness Scale (ESS), Insomnia severity index, BMI, FFM, body fat mass, waist circumference, and the waist-to-hip ratio.

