### Statistical assessment

To investigate if the data follows a normal distribution, we will use the Kolmogorov-Smirnov test. To compare qualitative data between the two groups, a chi-square test will be used. An independent t-test will be used to determine differences in quantitative data between groups. In non-parametric conditions and parametric conditions, the Wilcoxon test and paired *t*-test, respectively, will be used to compare the mean of quantitative variables within the group before and after the intervention. To compare the mean between the two groups, the Mann-Whitney test and *t*-test for non-parametric conditions and parametric conditions, respectively, will be used. Analysis of covariance will be utilized to determine the difference in data changes between the 2 groups at the end of the study. The adjusted *p-*values corresponding to each statistical test will be used to investigate the intervention effects by using the Bonferroni correction to analyze multiple outcomes. Data analysis will be done with SPSS software. We plan to conduct two subgroup analyses, both with strong biological rationale and possible interaction effects. Multiple regression model and analysis of covariance (ANCOVA) will be used to evaluate whether specific variables are confounders for the treatment effect and whether the treatment effect interacts with specific covariates.

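### The 80% power was computed at an unadjusted 5% level, but the outcomes are to be judged with Bonferroni-adjusted p-values; on the plan's own inputs, unadjusted for baseline, per-outcome power is then about 50% for eight primaries

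*Protocol article*

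**What the plan says.** **Sample size calculation (protocol article).** The inputs are fat-free mass (FFM) figures from an earlier trial: "63.4 and 3.4 (kg) in the intervention group and 66.9 and 4.9 (kg) in the control group". The section lists 15 outcome measures and concludes for them that "with an alpha error of 5% and power of 80%, 23 women will be needed in each group". The printed formula uses the 1 − α/2 normal quantile, so the test is two-sided. Recruitment is then raised for attrition: "We presume a drop-out rate of 20%, based on clinical study experience, and thus 28 women will be recruited in each group". Multiple testing is not mentioned.

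**Primary outcomes.** Eight variables are primary, each as a between-group difference in change from baseline: "Pittsburgh Sleep Quality Index (PSQI), Epworth Sleepiness Scale (ESS), Insomnia severity index, BMI, FFM, body fat mass, waist circumference, and the waist-to-hip ratio". The Secondary outcomes section adds seven more, making 15.

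**Statistical assessment.** Intervention effects are to be examined with adjusted p-values "by using the Bonferroni correction to analyze multiple outcomes". The number of outcomes in the correction is not given. The same section assigns analysis of covariance to the between-group difference in changes.

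**The concern.** The article makes two explicit choices that do not fit together. The size is set for a test at 5%, while the result is read from a test at 5% divided by the number of outcomes. Whichever natural family is meant, the per-outcome threshold is much stricter than the one behind the 80%.

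This is not a detail left to an unseen analysis plan. The power claim and the correction both stand in the article, and only the exact family could reasonably be settled elsewhere.

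What is at stake is how a non-significant result is read. This is a superiority trial, and its background section cites an earlier study that found no significant difference in sleep quality between the two kinds of diet. A second null result would be presented as coming from a trial with 80% power on each listed outcome, and no calculation in the document supports that.

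**Working it through.** **Inputs** (all from Sample size calculation unless noted)
- Difference in mean FFM: 66.9 − 63.4 = 3.5 kg.
- SDs 3.4 and 4.9 kg: sum of variances 11.56 + 24.01 = 35.57; root mean square SD √(35.57/2) = 4.217 kg; standardised difference 3.5/4.217 = 0.83.
- Two-sided 5%, power 80%, 23 per group evaluable, 28 recruited.
- Bonferroni (Statistical assessment). Two natural families: eight primaries, 0.05/8 = 0.00625; all 15 outcomes, 0.05/15 = 0.00333.

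**Step 1: reproduce the plan's figure.** n = (z₁₋α/₂ + z₁₋β)² × (σ₁² + σ₂²) / (μ₁ − μ₂)².

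At α = 0.05: (1.960 + 0.842)² × 35.57 / 3.5² = 22.79, rounded up to 23. This matches "23 women will be needed in each group". The denominator must be squared; the printed formula omits the square and would give about 80, a separate slip that does not affect this point.

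**Step 2: the same formula at the adjusted levels.**
- 0.05/8: (2.734 + 0.842)² × 35.57 / 12.25 = 37.1, so 38 per group.
- 0.05/15: (2.935 + 0.842)² × 35.57 / 12.25 = 41.4, so 42 per group.

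The stated 23 therefore cannot come from a 5% familywise level already divided among the outcomes.

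**Step 3: per-outcome power at the planned size.** Standard error with 23 per group: √(35.57/23) = 1.244 kg. Ratio: 3.5/1.244 = 2.814. Normal-approximation power is Φ(2.814 − z₁₋α/₂). The t-test column uses the noncentral t distribution with 44 degrees of freedom (54 with 28 per group).

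| Level | Critical z | 23 per group: normal / t | 28 per group: normal / t |
|---|---|---|---|
| 0.05 | 1.960 | 80% / 79% | 87% / 86% |
| 0.05/8 | 2.734 | 53% / 48% | 64% / 60% |
| 0.05/15 | 2.935 | 45% / 40% | 57% / 52% |

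The 28-per-group column treats every recruited woman as fully observed, which is generous.

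**Step 4: smaller families (assumed).** If the primaries were split by domain, the three sleep scores at 0.05/3 would have 66% / 63% power and the five body measures at 0.05/5 would have 59% / 55%, with 23 per group. With 28 per group the figures are 76% / 74% and 70% / 67%. None reaches 80%.

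**Step 5: detectable standardised difference.** With 23 per group and 80% power, by t-test: 0.84 SD at 0.05, 1.10 SD at 0.05/8 and 1.17 SD at 0.05/15.

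**Step 6: what ANCOVA would have to supply.** Read the stated SDs as unadjusted end-of-study SDs (an assumption). Adjusting for a baseline value with correlation r multiplies the variance by 1 − r². By the normal formula, 80% power with 23 per group needs 1 − r² = 23/37.1, so r ≈ 0.62 for eight outcomes, or 23/41.4, so r ≈ 0.67 for 15. The document gives no correlation. As an illustration at 0.05/8 (normal / t): r = 0.5 gives 70% / 65%, r = 0.7 gives 89% / 85%, r = 0.8 gives 98% / 96%.

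**The case against.** The strongest reply is that about 50% is not the power of the planned analysis. The primaries are changes from baseline and ANCOVA is planned for them, whereas the sample size inputs are FFM levels compared without adjustment. As Step 6 shows, a high enough baseline correlation would bring power back to 80% or beyond, even after Bonferroni.

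Three further points are fair. The family size is unstated, so 8 and 15 are readings, not facts. The figures are per outcome, and the chance of detecting at least one of several true effects is higher. The 0.83 SD comes from FFM and says nothing specific about the three sleep scores.

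All of this stands as a limit on the conclusion. A reader might infer that the trial lacks adequate power, or that it will miss a real effect about half the time. The documents do not support that: without a correlation and a stated family, the power of the planned analysis is unknown.

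None of it rescues the 80%. The sample size section takes no credit for ANCOVA, gives no correlation, and claims power for the listed outcome measures, not for at least one of them. Nor can Bonferroni itself be faulted for validity: it protects the type I error, and the harm is confined to an unsupported power claim.

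**Conclusion.** The point holds as an inconsistency between the sample size section and the statistical section. The 80% belongs to a single unadjusted test at 5%; the outcomes will be judged more strictly.

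On the plan's own inputs and its own unadjusted comparison, the shortfall in per-outcome power with 23 per group is roughly 27 to 31 percentage points for a family of eight (80% to 53%, or 79% to 48%) and 35 to 39 points for 15 (80% to 45%, or 79% to 40%). Analysing all 28 per group narrows the gap but does not close it.

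These sizes assume a true effect of 0.83 SD on the outcome in question, a family of 8 or 15, and no gain from baseline adjustment. The mismatch itself depends on none of these assumptions.

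**What to change.** 1. State which outcomes form the multiplicity family (the eight primaries, all 15, or another defined set).
2. In the sample size section, replace the 80% with the per-outcome power at the adjusted level: about 50% for eight primaries or 40–45% for 15, with 23 per group and labelled as unadjusted for baseline. Alternatively, give the detectable standardised difference at that level: about 1.10 SD for eight or 1.17 SD for 15. If credit is to be taken for ANCOVA, state the assumed baseline correlation and its source.
3. Replace Bonferroni with Holm. It controls the same familywise error and is never less powerful.

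The cost is wording in two sections and a less favourable power statement; no patients are added.

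Naming a single primary outcome tested at 5% is an option for the sponsor, not a required part of the fix. It is a design choice with its own cost: recruitment was due to end in late December 2022 and the article appeared on 16 January 2023, so demoting primaries now would be an outcome change after the planned recruitment period in an open-label trial.

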**Methods:**

This is an open-label randomized controlled trial to evaluate the effect of daily calorie restriction (control) and modified intermittent fasting (intervention) on sleep quality, anthropometric data, and body composition in women with obesity or overweight for 8 weeks. Fifty-six participants will be classified using stratified randomization based on body mass index (BMI) and age. Then, participants will be assigned to one of the two groups of intervention or control using the random numbers table. The sleep quality, daytime sleepiness, and insomnia will be evaluated by using the Pittsburgh Sleep Quality Index (PSQI), the Epworth Sleepiness Scale (ESS), and the Insomnia Severity Index respectively. The primary outcomes chosen for the study were as follows: the difference in sleep quality, daytime sleepiness, insomnia, BMI, fat-free mass (FFM), body fat mass, waist circumference, and waist-to-hip ratio from baseline to 8 weeks. Secondary outcomes chosen for the study were as follows: the difference in hip circumference, the visceral fat area, percent body fat, soft lean mass, skeletal muscle mass, extracellular water ratio, and total body water from baseline to 8 weeks.

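### Recruiting 28 women per group covers about 18% drop-out, not the stated 20%; the printed formula also lacks a square, a clerical slip that leaves the 23 unchanged

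*Protocol article*

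**What the plan says.** The Sample size calculation section of the protocol article takes fat-free mass (FFM) from an earlier randomized trial as its basis. For one arm, "The mean and standard deviation of FFM were 63.4 and 3.4 (kg) in the intervention group"; for the other, "66.9 and 4.9 (kg) in the control group". It then states that "with an alpha error of 5% and power of 80%, 23 women will be needed in each group". The allowance for losses follows directly: "We presume a drop-out rate of 20%, based on clinical study experience, and thus 28 women will be recruited in each group".

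The total of 56 is carried into the Abstract ("Fifty-six participants will be classified using stratified randomization") and into the Randomization and Intervention sections.

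The formula printed at the end of the section has the squared sum of the two normal quantiles times the sum of the two variances in its numerator. Its denominator is the plain difference in means, with no square.

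**The concern.** Two statements in the section do not agree with the figures around them.

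The first is the drop-out step. The protocol presents 28 as the consequence of needing 23 and losing 20%. If one in five of those recruited is lost, 28 is not enough to leave 23. The recruitment figure then misses the plan's own target at the plan's own drop-out rate, and the 80% power is not quite reached in the scenario for which the allowance was made.

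The second is the printed formula. Without the square, a reader who enters the stated means and standard deviations does not arrive at 23. What is at stake there is whether the published justification can be followed, not the size of the trial.

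**Working it through.** **Inputs**, all from the Sample size calculation section: means 63.4 and 66.9 kg (difference 3.5 kg); SDs 3.4 and 4.9 kg; alpha 5%, two-sided because the formula uses the quantile at 1 - alpha/2; power 80%; equal groups; drop-out 20%.

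**Step 1: reproduce the 23.** The usual normal-approximation formula, with the squared difference, is

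n = (z_0.975 + z_0.80)² x (SD1² + SD2²) / (difference)².

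- (1.960 + 0.842)² = 7.849
- 3.4² + 4.9² = 11.56 + 24.01 = 35.57
- 7.849 x 35.57 = 279.2
- 279.2 / 3.5² = 279.2 / 12.25 = 22.79, rounded up to 23

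The stated 23 is reproduced.

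**Step 2: the formula as printed.** Dividing by 3.5 instead of 12.25 gives 279.2 / 3.5 = 79.8 in absolute value. (With the means in the order listed, the difference is negative, and so is the result.) The units also fail: kg² divided by kg leaves a sample size in kg. The 23 was therefore obtained with the square, and only the printed expression lacks it.

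**Step 3: the drop-out allowance.**

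- Multiplying up: 23 x 1.2 = 27.6, rounded up to 28. This reproduces the stated figure.
- Dividing by the retained fraction: 23 / (1 - 0.20) = 28.75, rounded up to 29 per group, or 58 in total.
- Starting from the unrounded requirement does not rescue 28: 22.79 / 0.8 = 28.49, again 29.
- Expected completers from 28 at 20% loss: 28 x 0.8 = 22.4.
- Largest loss from 28 that leaves 23: 5 women, and 5/28 = 17.9%. A sixth loss (6/28 = 21.4%) leaves 22.

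**Step 4: what the shortfall costs in power.** The normal approximation is Φ(3.5 / √(35.57/n) - 1.960). The t-based figure uses the noncentral t distribution with 2n - 2 degrees of freedom and common SD √(35.57/2) = 4.217 kg.

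| Completers per group | Normal approximation | t-based |
|---|---|---|
| 23 | 80.4% | 78.6% |
| 22.4 | 79.3% | 77.5% |
| 22 | 78.6% | 76.7% |

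Within either column, the loss from 23 to 22.4 is about 1 point and the loss from 23 to 22 about 2 points.

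**The case against.** The strongest case on the other side is that none of this matters in practice. The shortfall is one woman per group; against the unrounded 22.79, the expected 22.4 is short by only about 0.4. A 20% drop-out rate is a round presumption, and 17.9% lies within the precision of such a guess. The Statistical assessment section itself expects very little loss to follow-up, and if nobody were lost, 28 per group would give 87.4% power by the normal approximation. Dropouts are also to be kept in the analysis through multiple imputation.

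Most of this stands as a statement about size: 28 is not materially wrong. It does not make 28 follow from 20%. The protocol draws that inference explicitly, and the arithmetic does not support it. An expectation of few losses is a reason to state a smaller allowance. Imputation keeps women in the analysis set, but does not by itself restore the outcome information that 23 completers would supply.

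Two stronger readings are tempting, and the document supports neither. A reader might infer from the printed formula that about 80 women per group are needed and that the trial is too small by a factor of 3.5. It is not: the standard formula gives 23 from the stated inputs, and the missing square affects only the printed expression. A reader might also set the t-based 77% against the nominal 80% and infer a loss of 3 points. That mixes two methods. By the t calculation, power is already 78.6% at the full 23; the remainder of the gap is the ordinary difference between the normal and t calculations, not an effect of drop-out.

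**Conclusion.** The concern holds as a small arithmetic error. At the stated 20% drop-out, 28 per group yields 22.4 expected completers against the required 23; 28 covers at most 17.9%. The shortfall is one woman per group (29 against 28, or 58 against 56), and the like-for-like power loss is about 1 to 2 points. The trial's size is not called into question.

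The missing square is a clerical error. Correcting it changes no sample size, power figure or analysis.

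The figures take the protocol's FFM means and SDs, equal groups and a two-sided 5% alpha as given. The t-based powers also assume a common SD and a pooled test. The 22.4 is an expectation; the actual number of completers per group will be a whole number, 23 after five losses and 22 after six.

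**What to change.** In the Sample size calculation section:

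1. Keep 56 women and make the allowance match, in one of two ways. Either state that 28 per group allows for about 18% drop-out (5 of 28), or keep 20% and state that about 22 completers per group are then expected, with about 79% power by the normal approximation. Each is a change of wording only, and the total of 56 stays correct wherever it appears.
2. Square the difference in means in the denominator of the printed formula. The 23 stays as it is.

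If the sponsor prefers to hold both 20% drop-out and 23 completers, the figure is 29 per group. That costs two more women in total, and 56 would become 58 in the Abstract and in the Randomization and Intervention sections. Given the size of the effect, this is not necessary.

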### Study hypothesis

We hypothesize that individuals with obesity or overweight will have more sleep disorders and that modified intermittent fasting diet will most benefit this group.

## Outcome measures

### Primary outcomes

The primary outcomes of the study are the differences between the two groups with regard to the changes from baseline values in the following variables: Pittsburgh Sleep Quality Index (PSQI), Epworth Sleepiness Scale (ESS), Insomnia severity index, BMI, FFM, body fat mass, waist circumference, and the waist-to-hip ratio.

### Secondary outcomes

The secondary outcomes of the study are the differences between the two groups with regard to the changes from baseline values in the following variables: the hip circumference, the visceral fat area, the percent body fat, the soft lean mass, the skeletal muscle mass, the extracellular water ratio, and the total body water.

### Intervention

The flow chart of the intervention is shown in Fig. 2. In this study, 56 participants will be selected from the Health Centers of Kashan University of Medical Sciences by Simple Random Sampling according to the inclusion and exclusion criteria. Eligible participants will be stratified by age and BMI to ensure between-group homogeneity. Participants per stratum will be assigned to one of the two groups “modified intermittent fasting” (intervention) and “daily calorie restriction” (control) after baseline investigations. All participants will be required to follow their diet which is prescribed for 8 weeks based on their group and daily energy requirements. The energy requirements for the individuals will be calculated using the Mifflin equation [18]. Intermittent fasting will involve alternating periods of feeding and fasting, on an every-other-day basis (subjects will consume only 25% of the recommended calorie intake on the fasting days and then will consume 100% of the calculated daily energy requirements on feeding days). At midnight each day, the fast and feed days will begin. All fast day meals will be consumed as lunch between 12.00 pm and 2.00 pm to ensure that each subject will be undergoing the same duration of fasting. Participants will be permitted to drink energy-free beverages (such as water, tea, and green tea), coffee without sugar (<400 mg caffeine daily), and non-starchy vegetables (such as lettuce, green leaf, cucumber, and tomato). They will be encouraged to consume plenty of water. On feeding days, the participants will be provided foods at 100% of the calculated daily energy requirements (three main meals and three snacks) and will be advised to eat breakfast at 8:00, lunch at 13:00, and dinner at 20:00. Additionally, participants will be advised to have the first snack at 10:00, the second snack at 16:00, and the last snack at 22:00. The control group daily will consume 63% of their energy requirement (three main meals and three snacks) and will be advised to eat breakfast at 8:00, lunch at 13:00, and dinner at 20:00. Also, the first snack should be eaten at 10:00, the second snack at 16:00, and the last snack at 22:00. Both groups will follow their diet for 8 weeks. Control and intervention group subjects must prepare all their meals at home. All subjects in the two groups will be asked to keep their regular physical activity throughout the study. Daily dietary carbohydrates, fat and protein will account for 55, 30, and 15% of energy requirement, respectively. All participants will have the same number of contacts with the dietician at the on-site visits and phone visits for questions. Implementation adherence will assess by a food record questionnaire. It will be completed by the participants once every 2 weeks, 3 days (2 days/week and 1-day weekend) a week. If the total caloric intake of patients will be between 80 and 110% of the prescribed, there will be adequate adherence [19]. The following will be prohibited during the study: taking a special diet, taking a special supplement or medicine. An overview of the study design, interventions, and assessments to be conducted during the study and their timing is presented in Fig. 1 (enrolment, interventions, and assessments) and Fig. 2 (flow chart of the intervention).

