### Plans for participant retention and adherence to the diet

To control the adherence to the diet by the participants, once every 2 weeks, food record questionnaires will be completed 3 days (two normal days and one day off) a week. Researchers will make regular phone calls to participants to reinforce what they will be doing and to encourage them to continue. Also, participants will be monitored in weekly phone interviews. The data of subjects who discontinue or deviate from intervention protocols for any reason will be analyzed with intention-to-treat.

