### Criteria for discontinuing or modifying allocated interventions

The criteria for discontinuing allocated interventions for a given trial participant include the following: calorie intake below 80% or above 110% of their recommended calorie, experiencing a severe emotional crisis during the study, and getting pregnant during the study.

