We propose to use two analysis sets; the intention-to-treat set, considering all patients as randomized regardless of whether they received the randomized treatment, and the “per protocol” analysis set. Given our expectation that very few patients will crossover or be lost to follow-up, these analyses should agree very closely. We will report reasons for withdrawal for each randomization group and compare the reasons qualitatively. The effect that any missing data might have on results will be assessed via sensitivity analysis of augmented data sets. Dropouts (essentially, participants who withdraw consent for continued follow-up) will be included in the analysis by regression imputation method for missing data. This will be accomplished using a set of repeated imputations created by predictive models based on the majority of participants with complete data. After the imputations are completed, all of the data (complete and imputed) will be combined and the analysis performed for each imputed-and-completed dataset. Rubin’s method of multiple (i.e., repeated) imputation will be used to estimate the treatment effect. No interim analyses will be performed.

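### The adherence rule checks total calories but not fasting, so a fasting-arm woman eating the control diet can be classed adherent, depending on which days she records

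*Protocol article*

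**What the plan says.** All of this is in the protocol article.

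- **Diets (Intervention).** On alternate days in the fasting arm, "subjects will consume only 25% of the recommended calorie intake on the fasting days", with 100% of requirement on the days between. For the comparator, "The control group daily will consume 63% of their energy requirement".
- **Adherence criterion (Intervention).** "If the total caloric intake of patients will be between 80 and 110% of the prescribed, there will be adequate adherence". The data come from a food record: "It will be completed by the participants once every 2 weeks, 3 days (2 days/week and 1-day weekend) a week". Days are chosen as weekday or weekend, not as fast or feed. The section on retention and adherence repeats the 3-day scheme in similar terms and adds that "participants will be monitored in weekly phone interviews".
- **Discontinuation (Criteria for discontinuing or modifying allocated interventions).** The same limits reappear as a ground for stopping the allocated diet: "calorie intake below 80% or above 110% of their recommended calorie".
- **Analysis sets (Statistical assessment).** Intention-to-treat and per-protocol sets are planned. The article comments: "Given our expectation that very few patients will crossover or be lost to follow-up, these analyses should agree very closely". It does not say who belongs to the per-protocol set.

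**The concern.** When two diets deliver almost the same energy, total energy cannot show which one a woman is following. The contrast lies in the pattern: very low intake every other day, taken as one midday meal. The stated criterion ignores that pattern, and the record need not contain both day types. A woman who drifts to a flat, control-like diet may therefore be counted as an adherent faster.

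Three things are at stake: the adherence the trial reports, the rule that stops a diet, and possibly the per-protocol analysis. If the band defined the per-protocol set, women who had in effect changed diet could remain in its fasting arm. Close agreement with intention-to-treat would then say little about whether fasting took place.

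**Working it through.** **Inputs (Intervention section).** Fast day 25%, feed day 100%, strict alternation; control 63% daily; band 80–110%; 3 days per record.

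**Step 1: energy match.** The fasting-arm average is (25 + 100)/2 = 62.5% of requirement. The stated control figure is 63%. The ratio is 63/62.5 = 1.008, so the arms are matched within 1%.

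**Step 2: flat 63% eater in the fasting arm, against the recorded days' prescription.** With k fast days among 3, the prescription is 25k + 100(3 − k) = 300 − 75k. Her intake is 3 × 63 = 189.

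| Fast days recorded | Prescribed | Score | Result |
|---|---|---|---|
| 0 | 300 | 189/300 = 63% | fails |
| 1 | 225 | 189/225 = 84% | passes |
| 2 | 150 | 189/150 = 126% | fails |
| 3 | 75 | 189/75 = 252% | fails |

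The same eating gives different verdicts according to the days written down. A fully compliant faster scores 100% in every row.

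**Step 3: how often (assumption: record days picked at random, both alternation starts equally likely).** Take two of five weekdays plus one of two weekend days. The weekday pair holds 0, 1 or 2 fast days with probability 0.2, 0.6, 0.2, and the weekend day is a fast day with probability 0.5. So k = 0, 1, 2, 3 has probability 0.10, 0.40, 0.40, 0.10; a one-day weekend gives the same. She passes 40% of single records, and 20% of records hold only one day type.

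Over an assumed four records:
- Judged one by one with independent days, she is never flagged with probability 0.4⁴ = 0.026. If the same weekdays are used each time this rises to 0.40, because 14 days is an even number and the day types repeat.
- Pooled, with K fast days in 12, she scores 756/(1200 − 75K). This is in band for K = 4, 5, 6 (84.0%, 91.6%, 100.8%), with probability 0.117 + 0.203 + 0.244 = 0.564 for independent records.

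The article states neither way of combining records, so the range is 2.6% to 56%.

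**Step 4: what the rule does catch.** With feed days at 100%, fast-day intake x breaches 110% as follows:
- one fast day: x + 200 > 247.5, so x > 47.5%
- two fast days: 2x + 100 > 165, so x > 32.5%

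Overeating on fast days with full feed days is therefore detected. Spreading the same energy over all days may not be.

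**The case against.** The strongest reply is that a condensed article cannot carry every operational detail: the denominator, the choice of days and the per-protocol definition may sit in a fuller document. That stands for those details taken singly. It does not cover the criterion itself, which is stated as total energy, is used again to stop the diet, and has no fasting component.

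A second reply is that the failure is narrow. The woman must eat near the control level every day, nothing in the article suggests this is common, and on the natural reading she fails most single records (60% under the assumption in the working). Staff reading a record would also see 63% on a fast day, and there are weekly calls. This limits the size of the problem, although no fasting criterion is attached to the calls or to the reading of records.

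A third reply is that the band may be meant day by day. She would then score 63/25 = 252% on fast days and 63/100 = 63% on feed days, and always fail. The article states no per-day rule, and its reference to a total points away from one.

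A reader might go further and infer that she always passes (63/62.5 = 100.8%) and that compliant fasters could have their diet stopped. Both need the band to be taken against the 62.5% average, which is printed nowhere. On that reading a perfect faster scores 160, 120, 80 or 40% with 0, 1, 2 or 3 fast days recorded, and would be rejected in 60% of records under the same assumption. That is too implausible a meaning of the rule to support either claim.

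**Conclusion.** The point holds in a limited form. The stated criterion does not check fasting, which is what separates two diets matched at 62.5% and 63% of requirement. Against the prescription of the recorded days, a flat 63% eater in the fasting arm is adherent with one fast day recorded (84%) and non-adherent with two (126%). That result needs only the protocol's own figures and that choice of denominator. The frequencies rest on assumed day selection and an assumed four records.

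The intention-to-treat comparison is not biased, since women are analysed as randomised whatever their adherence label. Reported adherence and the discontinuation criterion are affected. A reader might infer that the per-protocol analysis is compromised; the article does not define that set, so this follows only if the 80–110% band defines it. Severity is minor to moderate.

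**What to change.** 1. Keep the 80–110% band on total energy in both arms, and state that it is taken against the prescription of the recorded days.
2. Require every fasting-arm record to hold at least one fast and one feed day within the existing three.
3. Add a fast-day criterion for the fasting arm, for example mean fast-day intake of at most 37.5% of requirement, not counting the permitted vegetables and energy-free drinks. The value is a choice. It is where the protocol's own 110% limit falls on balanced days with full feed days: (x + 100)/2 = 1.10 × 62.5 = 68.75, so x = 37.5. The margin over 25% is 12.5% of requirement, or 188–263 kcal at an assumed 1,500–2,100 kcal.
4. Use the combined rule to report adherence and to define the per-protocol set.
5. In the discontinuation criteria, do not let the added fast-day limit alone stop a diet on a single record; two consecutive records outside it would be a reasonable trigger.

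Under this rule the flat eater always fails (63 > 37.5), and a compliant faster always passes (25% on fast days, 100% of the recorded days' total).

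The day-type check should be added to the band, not replace it. A day-type rule alone, with fast days at most 37.5% and feed days at 80–110%, would pass a woman at 37.5%/110% (147.5/125 = 118% of prescription on balanced days) and one at 0%/80% (80/125 = 64%). The band flags both.

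The cost is slightly more recording detail (a day-type label and some direction on which days to record) and probably a smaller per-protocol set in the fasting arm, which must meet an extra limit. No record day is added.
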